## **5.5 Subject Compliance**

Study subjects will record any interruptions of dosage in the weekly patient's diary and will be asked about compliance at each study visit/ telephone consultation.

## **5.6 Drug Accountability**

The responsible site personnel will use the study drug only within the framework of this clinical study and in accordance with this protocol. The hospital pharmacy is responsible for import and confirmation of receipt of study drugs, documentation of batches received and that the study drugs are securely stored under the advised temperature conditions. Study subjects will receive information on which tablet blister card no. they have been assigned to by the Viedoc system, and in what order the blister cards should be used, by the study team at visits. They will then collect the corresponding blister cards at the hospital pharmacy. The pharmacist dispensing the drugs will be responsible for the registration of batches delivered to patients. When a patient returns for the next visit, she will bring back the blister cards and any unused medication will be registered by the study team in the e-CRF and collected by the study team who will then return it to the pharmacy. At the return of study medication to the hospital pharmacy, the pharmacy will be responsible for destruction or disposal of any unused medicinal product and for recording this.

## **5.7 Drug Labeling**

The investigational product will have a label permanently affixed to the outside and will be labeled in Norwegian, in accordance with ICH GCP and national regulations. Labels will be prepared and affixed by Celgene after approval by [name]/ [name].

Label will include:

- a) Sponsor name, address and telephone number
- b) Name and telephone number of Principal Investigator (main contact)
- c) Information on pharmaceutical dosage form/ dosing instructions
- d) Batch number
  - Protocol number Celgene: AP-CL-LICPLAN-PI-12824
  - Protocol number sponsor: APGELP
  - EudraCT No: 2017-004116-19
- e) Patient’s enrolment code/ subject number
- f) Patient’s initials

- g) Name of prescribing doctor
- h) Date dispensed
- i) Period of use (expiry date)
- j) Storage conditions
- k) "For clinical trial use only"
- l) "Keep out of reach of children"
- m) Kit number

e)-h) will be blank spaces filled in by the investigators or pharmacist before dispensing the IMP to study subjects.

Note: Following Celgene's sale to Amgen of the global rights to Otezla®, rights and obligations under the contract with Celgene is transferred to Amgen from May 1, 2020.

## **5.8 Subject Numbering**

A unique subject number that is assigned when the subject signs the Informed Consent Form identifies each subject in the study. Once assigned, the subject number cannot be reused for any other subject.

## 6 STUDY PROCEDURES

### 6.1 Table 3. Trial flow Chart

| Visits/ procedure         | Screening       | Baseline
Inclusion | Visit 2 | Telephone
interview | Telephone
interview | Visit 3 | Telephone
interview | End of
treatment
visit | Withdrawal
visit  |
|---------------------------|-----------------|-----------------------|---------|------------------------|------------------------|---------|------------------------|------------------------------|----------------------|
| Week +/- 7 days           | Max
-90 days | 0                     | 4       | 8                      | 12                     | 16      | 20                     | 24                           | Max 14 days
after |
| Informed consent          | x               |                       |         |                        |                        |         |                        |                              |                      |
| Eligibility
assessment | x               |                       |         |                        |                        |         |                        |                              |                      |
| Randomisation             |                 | x                     |         |                        |                        |         |                        |                              |                      |
| Compliance                |                 |                       | x       | x                      | x                      | x       | x                      | x                            | x                    |
| Medical history           | x               | x                     | x       |                        |                        | x       |                        | x                            | x                    |
| Safety evaluation         | x               | x                     | x       | x                      | x                      | x       | x                      | x                            | x                    |
| Clinical examination      | x               | x                     | x       |                        |                        | x       |                        | x                            | x                    |
| Weight                    | x               | x                     | x       |                        |                        | x       |                        | x                            | x                    |
| PGA                       |                 | x                     |         |                        |                        | x       |                        | x                            | x                    |
| PtGA                      |                 | x                     |         |                        |                        | x       |                        | x                            | x                    |
| DLQI                      |                 | x                     |         |                        |                        | x       |                        | x                            | x                    |
| FSDS-R                    |                 | x                     |         |                        |                        | x       |                        | x                            | x                    |
| GHQ-28                    | x               | x                     | x       |                        |                        | x       |                        | x                            | x                    |
| GELP score                | x               | x                     | x       |                        |                        | x       |                        | x                            | x                    |
| Vulval/
vaginal biopsy |                 | x                     |         |                        |                        |         |                        | x                            |                      |
| Hcg           | x               | x                     | x       | x                      | x                      | x       | x                      | x                            | x                    |
| GFR           | x               |                       |         |                        |                        |         |                        |                              |                      |
| IGRA          | x               |                       |         |                        |                        |         |                        |                              |                      |
| Collect patient diary     |                 |                       |         |                        |                        | x       |                        | x                            |                      |
| Clinical photo            |                 | x                     |         |                        |                        |         |                        | x                            |                      |

 Blood or urine (HCG) sample

## 6.2 By Visit

The study comprises the following visits, study procedures and assessments:

### **Screening:**

Medical history, eligibility assessment  
Clinical examination  
Weight  
Safety evaluation  
GELP, GHQ-28, HCG, GFR, IGRA  
Informed consent

### **Baseline visit (week 0):**

Randomization and initiating apremilast or placebo treatment  
Medical history including current use of topical steroid (no of days used per week last 4 weeks).  
Clinical examination  
Weight  
Safety evaluation  
Clinical photo  
PGA, GELP, PtGA, FSDS-R, DLQI, GHQ-28  
Vulval and/ or vaginal biopsy

### **Visit 2 (week 4):**

Compliance, medical history  
Clinical examination  
Safety evaluation  
Weight  
GELP, GHQ-28

**Telephone interview (week 8):** Compliance, safety evaluation

**Telephone interview (week 12):** Compliance, safety evaluation.

### **Visit 3 (week 16):**

Compliance, medical history.  
Clinical examination  
Weight  
Safety evaluation  
PGA, GELP, DLQI, FSDS-R, GHQ-28, PtGA  
Collect patient diary

**Telephone interview (week 20):** Compliance, safety evaluation

### **Visit 4 (week 24):**

Compliance, medical history  
Clinical examination  
Weight  
Safety evaluation  
Clinical photo

PGA, GELP, PtGA, DLQI, FSDS-R, GHQ-28  
Collect patient diary  
Vulval/vaginal biopsy

### **Informed consent**

Each subject must have given informed consent voluntarily before any study specific procedures are initiated.

### **Study concept/method**

Inclusion will take place in a 12 months period. Patients must sign consent forms to participate and will receive oral and written information about the project and their right to withdraw from the study at any time.

Before enrolment patients will be screened for eligibility. Case history and use of medication will be registered. During all visits, clinical examination and safety monitoring will be performed. Extragenital LP will be registered.

### **Treatment phase**

After inclusion, patients will be randomized to either oral apremilast or matching placebo, starting at week 0. After initial standard titration of dose day 1-6, standard dose of 30 mg apremilast b.i.d. or placebo is used for 24 weeks. Patients and investigators are blinded to treatment allocation throughout the study period.

### **Telephone interviews:**

At week 8, 12 and 20, participants will be contacted by phone by a research nurse and asked about possible side effects, compliance, and will be encouraged to fill in the diary log. The interview will specifically focus on any psychiatric side effects. For WOCBP, the result of the home pregnancy test will be recorded.

### **Clinical assessments**

Clinical assessments will consist of registering GELP score, clinical photos of target area, and Physician Global Assessment (PGA) score(30) for evaluation of the clinical grade of GELP. In addition, Patient's Global Assessment (PtGA)(30), Dermatology Life Quality Index (DLQI) score, General Health Questionnaire (GHQ-28) and Female Sexual Distress Scale (FSDS-R) will be recorded.

### **Clinical status/ examination:**

- Inspection of the genital area, the cavum oris and, if relevant, other affected skin areas
- Blood pressure
- Cardiac and pulmonary auscultation

**Patients' weekly assessment:** All patients will receive a diary at baseline for weekly registration of steroid use (no. of days per week), genital pain assessment (VAS scale 0-10) and adverse events. The diary is collected at week 16 and week 24. Participants may also use ViedocMe weekly for electronic registration.

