## **2.2 Secondary Endpoints**

2. Mean GELP score improvement from week 0 to week 24 in all patients
3. Weekly use of topical steroid, collected from patient diary
4. Weekly VAS pain score, collected from patient diary
5. Number of patients with GELP score improvement at week 16 and 24
6. Separate GELP score assessments: Area of involvement (in cm^2), number of erosions, erythema, striae and pain (VAS) at week 4, 16 and 24
7. Physician Global Assessment (PGA) and Patient Global Assessment (PtGA) scores at week 0, 16 and 24
8. Selected QoL measures (DLQI, GHQ-28) at week 0, 16 and 24
9. Sexual function assessments (FSDS-R) at week 0, 16 and 24

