#### **10.5.4 Secondary analyses**

Continuous secondary outcomes at 4-, 16- and 24-weeks follow-up will be assessed using the same statistical principle as for the primary outcome, i.e. an ANCOVA model adjusting for the measured outcome at baseline. Categorical outcomes will be assessed with Pearson chi-square tests or logistic regression models as appropriate. In addition, statistical analysis using mixed models for repeated measurements will be conducted.

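### Weekly diary pain has no scheduled pre-treatment value for its baseline-adjusted ANCOVA, and diary collection is not scheduled at the withdrawal visit

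*Protocol*

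**What the plan says.** Section 2.2 lists "Weekly VAS pain score, collected from patient diary" as a secondary endpoint, next to weekly topical steroid use from the same diary.

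Section 6.2 (Patients' weekly assessment) describes the diary: "All patients will receive a diary at baseline for weekly registration of steroid use (no. of days per week), genital pain assessment (VAS scale 0-10"), together with adverse events. Electronic entry through ViedocMe is optional. The baseline visit in section 6.2 is also the start of treatment: "Randomization and initiating apremilast or placebo treatment". That visit takes a retrospective value for steroid use, "Medical history including current use of topical steroid (no of days used per week last 4 weeks"), and no matching item for pain.

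For continuous secondary outcomes at weeks 4, 16 and 24, section 10.5.4 prescribes "an ANCOVA model adjusting for the measured outcome at baseline". It adds mixed models for repeated measurements.

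On collection, section 6.2 states "The diary is collected at week 16 and week 24". In Table 3 (section 6.1) the row "Collect patient diary" is marked at weeks 16 and 24 and is empty in the withdrawal column. Section 6.3, on the withdrawal visit, does not mention the diary.

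**The concern.** Two gaps in the visit schedule bear on the diary endpoints, and a statistical analysis plan cannot close either one afterwards. It can choose a model, but it cannot create a pre-treatment value that was never taken or recover a diary that was never collected.

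The first gap concerns precision. With 21 patients per arm, chance differences in baseline pain are likely enough to matter, and adjusting for the same measure at baseline is the usual way to deal with them. The protocol intends this adjustment and provides for it with steroid use, but not with pain.

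The second concerns completeness. Patients who leave the study early may differ in tolerability or response from those who stay, and theirs are the diaries with no scheduled collection. The same diary also holds patient-recorded adverse events and, under section 5.5, dosing interruptions. Both are also asked about at visits and calls, so for these it is the weekly record that is at risk.

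**Working it through.** **The plan's own figure.** The protocol gives no precision figure for the diary endpoints. Its sample size concerns the primary endpoint (section 10.1: difference 4, SDs 4.5 and 4.2, 80% power, 5% level, taken as two-sided). The common SD is √((4.5² + 4.2²)/2) = 4.353. Exact t-test power is 78.7% with 19 per group and 80.8% with 20, so the stated 20 per group is reproduced. Nothing below alters it.

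**Baseline values, side by side.**

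| Measure | Pre-treatment value scheduled? | Source |
|---|---|---|
| Diary steroid use | Yes, recall over the last 4 weeks | 6.2, baseline visit |
| Diary pain (weekly, VAS 0–10) | None scheduled; date of first entry not stated | 6.2, weekly assessment |
| GELP pain item (VAS, on pressure) | Yes, at screening and baseline, vulva and vagina scored separately | 6.1 and 7.1, Table 4 |

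If the first diary entry is made at the end of week 1, it follows the start of treatment. The full dose begins on day 6 under section 5.1. Such an entry is post-randomisation and cannot stand in for a baseline.

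**Precision cost.** The documents give no correlation ρ between baseline and follow-up diary pain, so ρ is assumed. Relative to an analysis adjusted for the same measure, an unadjusted analysis has variance ratio 1/(1 − ρ²) and SE ratio 1/√(1 − ρ²):

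| ρ (assumed) | Variance ratio | SE ratio |
|---|---|---|
| 0.3 | 1/0.91 = 1.10 | 1.05 |
| 0.5 | 1/0.75 = 1.33 | 1.15 |
| 0.7 | 1/0.51 = 1.96 | 1.40 |

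If the proxy is used and its correlation with follow-up diary pain is r, the SE ratio becomes √((1 − r²)/(1 − ρ²)). Two illustrations, with r also assumed:

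- ρ = 0.5, r = 0.3: √(0.91/0.75) = 1.10 instead of 1.15.
- ρ = 0.7, r = 0.5: √(0.75/0.51) = 1.21 instead of 1.40.

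**Entries at stake on withdrawal from the study.** This is for a paper-only patient who does not hand in her diary, at one entry per week:

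| Leaves at week | Entries collected | Entries not collected |
|---|---|---|
| 4 | 0 | 4 |
| 8 | 0 | 8 |
| 12 | 0 | 12 |
| 15 | 0 | 15 |
| 20 | 16 | 4 |
| 23 | 16 | 7 |

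One patient is 1/42 = 2.4% of the trial. The protocol gives no dropout rate; going from 20 to 21 per group allows for 1 − 40/42 = 4.8%.

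**The case against.** The strongest reply is that these are small gaps on supportive endpoints and that the protocol offers ways around both.

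- **The analysis is not impossible.** A reader might infer that no pre-treatment diary pain can exist and that ANCOVA is ruled out. The protocol does not date the first entry, so a week-0 entry is not excluded. A pain VAS is taken at baseline within the GELP score and can serve as a covariate. The mixed model in section 10.5.4 does not strictly need a baseline diary value. All of this stands. It remains that the covariate section 10.5.4 names, the same outcome at baseline, is not scheduled for diary pain, and that no substitute is named.
- **The precision loss may be small.** The ratios above compare full adjustment with none and rest on an assumed ρ. At ρ = 0.3 the SE rises by only 5%, and a proxy recovers part of any loss. A reader might turn ρ² at 0.5 and 0.7 into a loss of 25% to 49% of the sample. The documents do not support that as an estimate, because they give no ρ and a proxy is available. Randomisation also keeps the unadjusted comparison unbiased.
- **Losing a whole diary needs several conditions together.** The patient must leave the study, not only treatment, before week 16, use paper only, and not hand the diary over. Section 6.5.1 keeps patients who stop treatment in the visit schedule. It also calls the final assessment offered to withdrawn patients an end of study visit, and the week 24 visit does collect the diary. This narrows the problem. It does not remove it, because Table 3 has a separate withdrawal column in which the diary cell is empty, and section 6.5 allows a patient to leave both treatment and assessments voluntarily.
- **Missing data are left to the analysis plan.** Section 10.5.6 defers their handling, but the visit schedule that determines which data exist is fixed in the protocol.

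**Conclusion.** Both gaps are real and modest. As scheduled, the data do not supply the same-measure covariate that section 10.5.4 calls for in the case of diary pain; only a proxy measuring pressure-induced pain is available. Diary collection is not scheduled at the withdrawal visit, so all entries can be lost for a paper-only patient who leaves the study before week 16 without returning the diary, and the entries since week 16 for one who leaves later.

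The SE for diary pain without adjustment would be 1.05 to 1.40 times the adjusted one for assumed ρ between 0.3 and 0.7, and less with the proxy. The number of patients whose diaries would be lost cannot be estimated from the protocol.

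A reader might go further and infer that the trial's main result is weakened. It is not: the primary endpoint, its ANCOVA and the sample size do not use the diary, and section 10.5.1 classes all other efficacy analyses as supportive or exploratory. The point is worth correcting because the correction is cheap and cannot be made after the fact.

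**What to change.** 1. **Baseline pain.** Add one diary-type VAS entry for genital pain over the past week at the baseline visit, completed before the first dose. Mark it in Table 3 and name it as the ANCOVA covariate for diary pain.
2. **Patients already enrolled.** The synopsis gives 24.09.2019 as the date of first enrolment, so some patients may lack this entry. In that case use the baseline GELP pain VAS as the covariate for all patients, and do not mix two different pain measures in one covariate. Because vulva and vagina are scored separately, state before unblinding how the two site values enter the model.
3. **Withdrawal visit.** Mark diary collection in the withdrawal column of Table 3 and state it in sections 6.2 and 6.3.

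The cost is one extra VAS line at an existing visit, one mark in the flow chart and a sentence in each of two sections. If the proxy has to be used, the remaining drawback is an imperfect covariate that recovers only part of the precision.

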### **6.3 Withdrawal Visit**

All patients who withdraw from the study will be offered an appointment with one of the participating clinicians ([name] or [name]) 7-14 days after withdrawal. If the patient is willing to state her reason for withdrawal, the reason for withdrawal will be registered.

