### **6.4 After End of Treatment (Follow-up)**

At the end of study at week 24 or if earlier withdrawal from study, patients will be given an appointment with one of the participating clinicians ([name] or [name]) after approximately 3-6 months, for regular clinical follow-up.

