## **Procedures for Discontinuation**

### **6.5.1 Patient Discontinuation**

Patients who withdraw or are withdrawn from the study, will stop further treatment with the IMP. The reason for discontinuation shall be recorded if the patient agrees. Patients who are withdrawn from the study will be offered a final assessment (end of study visit) and will continue standard clinical follow-up at the Vulva clinic.

The investigators will follow up any significant adverse events until the outcome either is recovered or resolved, recovering/resolving, not recovered/not resolved, recovered/resolved with sequelae, fatal or unknown.

All patients randomized will be included in the study population. Patients who withdraw or are withdrawn from the study after randomization cannot be replaced.

Patients who are withdrawn from treatment will continue study visits and assessments as described in this protocol.

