## **10 STATISTICAL METHODS AND DATA ANALYSIS**

### **10.1 Determination of Sample Size**

Helgesen et al.(10) found in a randomized trial a comparable effect of photodynamic therapy and topical corticosteroid, with mean GELP score reduced from 11 (standard deviation 4.5) at baseline to 7 (standard deviation 4.2) after 24 weeks follow-up. We assume a similar mean difference and standard deviation in GELP score at week 16 between apremilast-treated patients and placebo-treated patients as between the baseline and 24 weeks measurements in the previous trial reported by Helgesen et al.

To obtain 80% statistical power from an independent samples t-test with 5% significance level, mean difference of 4 and standard deviations in the two groups of 4.5 and 4.2, 20 subjects are required in each group. Based on this sample size calculation, and to account for a small drop out rate, we want to include 21 patients in both the apremilast and the placebo-treated group, i.e. 42 patients included in total.

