### **10.5 Statistical Analysis**

#### **10.5.1 Statistical Hypothesis**

This protocol is designed to establish the superiority of apremilast compared to placebo treatment on disease activity measured by GELP score after 24 weeks treatment in patients with moderate to severe female genital erosive lichen planus.

The primary null hypothesis is that there is no difference between the treatment groups in GELP score after 24 weeks treatment.

The primary alternative hypothesis is that there is a difference between the treatment groups in GELP score after 24 weeks treatment.

There is only one identified primary hypothesis test in this trial. All other efficacy analyses will be regarded as supportive or exploratory.

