#### **10.5.6 Missing data and intercurrent events**

If missing data is regarded as having a significant effect on the conclusions of the trial, sensitivity analyses with different methods for handling missing data will be included. Such methods may include complete case analyses, last observation carried forward, worst case/best case imputation and multiple imputation techniques. Statistical analysis with mixed models for repeated measurements will also be conducted to obtain robust estimates in case of missing data.

Other intercurrent events, such as the use of rescue topical steroid crème, might also influence the conclusion of the trial.

The precise handling of missing data and other intercurrent events affecting the efficacy interpretation of the trial results will be detailed in the statistical analysis plan.

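### Patients who leave the study are not asked for a GELP score at week 24, although the primary endpoint needs one from every randomised patient and a suitable clinic appointment often exists

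*Protocol*

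**What the plan says.** Section 2.1 sets the primary endpoint as the GELP score at week 24 by arm. Section 10.3 defines the ITT population as everyone randomised, whether or not they adhered.

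Section 6.5 separates two routes:
- **Leaving the study:** the patient's own choice, loss to follow-up, or the principal investigator's judgement that continued participation endangers her.
- **Stopping treatment but not assessments:** the principal investigator's safety judgement, incorrect enrolment, or pregnancy.

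Under section 6.5.1 the second group keeps the full visit schedule. The first group stops study drug, cannot be replaced, and is offered a last visit, which is described in three places:
- Section 6.3 names no assessments and puts it "7-14 days after withdrawal. If the patient is willing to state her reason for withdrawal, the reason for withdrawal will be registered".
- Table 3 (section 6.1) allows at most 14 days, with no lower limit, and marks a GELP score.
- Section 6.5.1 gives no timing: "Patients who are withdrawn from the study will be offered a final assessment (end of study visit").

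For later care, section 6.4 says that "patients will be given an appointment with one of the participating clinicians" after about 3-6 months, as ordinary clinical follow-up. No trial assessment is attached to it.

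**The concern.** A patient who leaves the study has her final GELP score tied to the day she left. For most withdrawal times it shows neither her response on drug nor her state at week 24. Scheduled GELP scores between baseline and week 24 exist only at weeks 4 and 16, so someone leaving at week 14 has no scheduled on-drug score after week 4. If she declines the offered visit, her last score is from week 0, 4 or 16.

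The statistical analysis plan can choose how to treat a missing score, but it cannot recover one that was never collected. Collection is fixed in this protocol.

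The split in section 6.5 adds to the problem. Safety as judged by the principal investigator appears under both routes, so two similar patients could be classified differently, one keeping her week-24 score and the other losing it. If leaving is related to treatment or to disease course, the week-24 comparison then rests on a selected subset, or on assumptions about the rest.

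**Working it through.** **Inputs.** Visit window ±7 days (Table 3), so week 24 means weeks 23-25. Withdrawal visit 7-14 days after withdrawal (section 6.3) or 0-14 days (Table 3). Routine appointment about 3-6 months later (section 6.4), read here as counted from withdrawal. One month = 52.18/12 = 4.35 weeks, so 3-6 months = 13.0-26.1 weeks. Let w be the study week of withdrawal.

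**Step 1: can the withdrawal visit serve as week 24?** Under section 6.3 it falls at weeks w+1 to w+2, under Table 3 at w to w+2. Either reaches week 23 only if w + 2 ≥ 23, so w ≥ 21.

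**Step 2: can the section 6.4 appointment serve as week 24?** It falls at weeks w+13.0 to w+26.1. The late end always reaches week 23. The early end must not pass the window:
- w + 13.0 ≤ 25 gives w ≤ about 12 (inside the window).
- w + 13.0 ≤ 24 gives w ≤ about 11 (on week 24 itself).

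| Withdrawal week | Section 6.3 visit (weeks) | Section 6.4 appointment (weeks) | Can either meet weeks 23-25? |
|---|---|---|---|
| 4 | 5-6 | 17-30 | Section 6.4 |
| 8 | 9-10 | 21-34 | Section 6.4 |
| 11 | 12-13 | 24-37 | Section 6.4, at its earliest |
| 16 | 17-18 | 29-42 | Neither |
| 20 | 21-22 | 33-46 | Neither |
| 22 | 23-24 | 35-48 | Section 6.3 |

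As written, only the withdrawal visit carries a GELP score, so withdrawals before about week 21 give no week-24 value. Using the section 6.4 appointment would cover withdrawals up to about week 11-12. Between about weeks 12 and 21 neither visit fits, and the appointment would have to be dated to week 24.

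**Step 3: do the three descriptions agree?** The lower limit is day 7 in section 6.3, day 0 in Table 3 and absent in section 6.5.1. Table 3 also separates the withdrawal visit from the end of treatment visit: biopsy, diary collection and photograph are marked only for the latter. Section 6.5.1's label does not say which list applies.

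**Step 4: is power the argument?** The plan's sample size reproduces. With "mean difference of 4 and standard deviations in the two groups of 4.5 and 4.2, 20 subjects are required in each group", the pooled SD is √((4.5² + 4.2²)/2) = 4.35, and a two-sided 5% t-test has 80.8% power at 20 per group (78.7% at 19). With 21 per group and three per arm excluded (18 left), power is 76.4%. Suppose instead that three apremilast leavers are kept at 21 per arm, with placebo and the SDs unchanged:
- Each loses 2 points of effect: difference 4 − 3×2/21 = 3.71, power 77.0%.
- Each loses all 4 points: difference 4 − 3×4/21 = 3.43, power 70.2%.

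The three leavers and their loss of effect are assumptions. Recovered off-drug scores bring little or no power.

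**The case against.** **The gap is narrow.** This stands. Patients who stop treatment only are already followed to week 24, and those lost to follow-up cannot be asked. The point concerns patients who leave by choice or by the investigator's decision.

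**A week-24 score from an early leaver is even further off drug than the withdrawal score.** True: about 13 weeks for someone who leaves at week 11. But the same applies to patients who stop treatment and stay on schedule, whose week-24 score the protocol wants. An analysis of all randomised patients whatever their adherence calls for that score.

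**Mixed models for repeated measurements are planned.** They can use weeks 4 and 16, but they then rest on an assumption about the unseen week-24 value, which an observed score would replace.

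**The wording mismatch is small.** Also fair. The 7-14 day window lies inside 0-14 days, and an end of study visit need not be Table 3's end of treatment visit. Alone this would be clerical.

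**Stronger readings to avoid.** A reader might infer that the off-drug withdrawal score will be carried forward as the week-24 value and bias one arm. The protocol does not say so. Of sensitivity analyses it says "Such methods may include complete case analyses, last observation carried forward", among others, and leaves the precise handling to the statistical analysis plan. A reader might also infer that every withdrawal score is taken at least a week off drug. The visit is only offered, and Table 3 allows day 0. Nor does recovering scores restore the planned power, as step 4 shows.

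**Conclusion.** The point holds as a low-cost improvement. For patients who leave the study before about week 21, the protocol requests no GELP score at the primary time point, while its analysis population includes them. The case rests on collecting the outcome that the all-randomised comparison needs.

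Its size depends on how many patients leave, for which the protocol gives no rate. The allowance from 20 to 21 per group covers one loss per arm, and each leaver is 1/21 = 4.8% of an arm. No figure for bias can be derived from the document.

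Two assumptions matter: that the 3-6 months in section 6.4 run from withdrawal, and that the statistical analysis plan can use a score obtained after a patient has left. If that plan chose an analysis of on-treatment response only, the score would matter less, but collecting it keeps both options open.

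**What to change.** Add to sections 6.3 and 6.4 that a patient leaving the study is asked whether one GELP score may be recorded at her original week 24 (±7 days) for the ITT analysis. Use the section 6.4 appointment where it fits (withdrawal up to about week 11-12), and otherwise date that appointment to week 24. Show this in Table 3. For withdrawals from about week 21 on, the withdrawal visit may already serve.

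Reconcile the timing, name and content of the withdrawal visit across section 6.1 (Table 3), section 6.3 and section 6.5.1. State in section 6.5 how an investigator's safety decision is assigned to one route or the other.

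The cost is protocol and consent wording and an earlier appointment for later leavers. The clinicians and the appointment are already in the plan. Some patients will refuse, so the gap would shrink but not close.
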